#### Economic evaluation

The study population and the selection criteria will be the same as those in the quantitative quasi-experimental design.

### Participant timeline

The participants will be contacted by telephone to arrange and appointment, in with the person will be informed individually about the study. After agreement, he/she will sign the informed consent form and complete the baseline questionnaire (December–January 2015). Those participants not able to arrange an appointment, will receive the consent form and complete the baseline questionnaire during the first session of the intervention (just before starting). The intervention will last 22 weeks (January–June 2015). At the end of the last session the participants will complete the follow-up questionnaire (June 2015). Regarding the qualitative analysis, the in-depth interviews and focus groups will be carried out between 6 to 9 months after the intervention (January–March 2016).

The participant flowchart of the study procedure is outlined in Fig. 1.

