## Methods

### Study design

This is a mixed methods multi-approach evaluation that includes:a qualitative evaluation among coordinators and participants who underwent the intervention through in-depth interviews and focus groups, respectively;a quantitative quasi-experimental design, comparing a group of individuals taking part in the intervention (IG) with another group with similar characteristics not receiving the intervention (CG). Data will be collected at the beginning and at the end of the intervention;an economic evaluation, which includes a cost-utility analysis.

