#### Quantitative quasi-experimental design

The study population will consist of adults aged 65 years or older residing in the disadvantaged neighborhoods of Barcelona (Spain) selected for the study. The intervention neighborhoods (*n* = 2) and comparison neighborhoods (n = 2) will be selected on a convenience basis, ensuring similar socioeconomic characteristics, including the percentage of people with primary studies or less, unemployment rates and disposable household income rates.

The intervention will be offered to adults aged 65 years or older, living in one of the two selected neighborhoods, and recruited through primary care centers, social services and civic centers for older people. Once individuals have accepted to participate, there will be a pre-registration process that will record their names and telephone numbers. Later, the participants will be contacted by telephone to arrange an appointment, in which the person will be informed individually about the study. After agreement, he/she will sign the informed consent form and complete a questionnaire.

To calculate the sample size, we took into account that 45% of people aged 65 years or more in Barcelona reports fair or poor health [21] and assumed that the intervention would reduce this prevalence by 17 points. Accepting an alpha risk of 0.05% and a power of 80% in a unilateral contrast, and assuming a loss of 10%, we estimated that a theoretical sample of 79 participants in the IG and 79 participants in the CG will be needed.

We expect to recruit 80 individuals in the IG and 80 in the CG. To have similar groups, the recruitment settings (primary care centers, social services and civic centers) would be taken into account, by selecting the same percentage of people from each setting.

The exclusion criteria are the following:Participants with difficulties in maintaining participation for 6 months.Participants with difficulties in understanding or expressing themselves in Spanish or Catalan.

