#### Quantitative quasi-experimental design

##### Main outcomes

Social support will be measured through questions taken from the Medical Outcomes Study: Measures of Quality of Life Core Survey (MOS) [22] and NSHAP questionnaires [20]. Psychological morbidity will be measured through Goldberg’s General Health Questionnaire (GHQ-12) [23], and health-related quality of life will be measured through the EuroQoL (EQ-5D) questionnaire [24]. Objective information will be obtained on visits to the primary care center during the year before and after the intervention through access to the electronic records of the primary care centers.

All these variables will be measured simultaneously in individuals in the IG and CG. Data will be collected through baseline and post-intervention questionnaires administered by trained researchers.

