##### Intervention-related variables

We will register attendance of participants at each session in the IG. Additionally, at the end of the School of Health, we will measure participants’ satisfaction with questions such as “please rate your general satisfaction with the School of Health from 0 to 10;”“ please rate your satisfaction with the speakers, place/space, frequency, schedule, and length of sessions from 0 to 10” “ Would you recommend the School of Health to a friend? ” These questions will be included in the post-intervention questionnaire.

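### Intervention-group follow-up is tied to the last session with no stated route for absentees, so the questionnaire outcomes risk comparing attenders with a comparison group that has no such filter

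*Protocol article*

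**What the plan says.** Under Participant timeline, the follow-up occasion is: "At the end of the last session the participants will complete the follow-up questionnaire (June 2015". The same section does provide an alternative at baseline: "Those participants not able to arrange an appointment, will receive the consent form and complete the baseline questionnaire during the first session of the intervention". It gives nothing parallel for follow-up.

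Study design describes the CG as "another group with similar characteristics not receiving the intervention (CG"), so the last-session rule can apply only to the IG. For the CG, Main outcomes promises common timing, "All these variables will be measured simultaneously in individuals in the IG and CG", and a common mode, "Data will be collected through baseline and post-intervention questionnaires administered by trained researchers". It does not say where or how CG members are reached.

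Three other statements matter here:
- Visits are taken from electronic records and do not depend on the session (Main outcomes): "Objective information will be obtained on visits to the primary care center during the year before and after the intervention through access to the electronic".
- Contact details exist for people who accept the intervention: "there will be a pre-registration process that will record their names and telephone numbers" (Study setting and participants, quantitative design).
- Absentees can be identified: "We will register attendance of participants at each session in the IG" (Intervention-related variables).

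**The concern.** Whether an outcome is observed should not depend on taking up the intervention in one group only. Here the only stated IG follow-up occasion is itself part of the programme, so someone who left early or was away on the final day has no stated way of giving a follow-up value.

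The planned analyses do not repair this. The McNemar, paired t and sign tests, the two-sample McNemar comparison and the Poisson models all need a follow-up value. Adjusting for the pre-intervention value and for characteristics that differ at baseline, which the plan does only for outcomes that differ between groups at baseline, deals with selection on those variables. It does not deal with selection on what happened after baseline. The limitations section mentions short follow-up and group differences, but not this.

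At stake are the group comparison on the questionnaire outcomes, the QALY difference in the cost-utility ratio, and the satisfaction ratings, which would omit those who left.

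**Working it through.** **Inputs from the article.** Target of 80 per group; assumed loss of 10%, one figure for both groups; fair or poor health in 45%; assumed reduction of 17 points, that is, to 28%.

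**Inputs assumed.** The article gives no attrition rate and no outcome information for non-attenders. I take the missing IG fraction *m* as 10-40%, and the shortfall *g* in absentees' change relative to attenders as 0, 10 or 20 points. CG loss is taken as unrelated to outcome.

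**The plan's own sample size.** Reading the printed alpha of 0.05% as 0.05, one-sided, with 80% power:

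n = [1.645·√(2·0.365·0.635) + 0.842·√(0.45·0.55 + 0.28·0.72)]² / 0.17² ≈ 98.1, so 99 evaluable and 99/0.90 = 110 enrolled per group.

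The stated 79 is not reproduced. That is a separate matter. Only the 17 points, the 10% and the 80 are used below.

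**Bias in the change.** Let attenders change by *A* (improvement positive). The whole group changes by (1−m)·A + m·(A−g) = A − m·g. Measuring attenders only therefore overstates the IG change by m·g:

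| m | g = 0 | g = 10 | g = 20 | m·20 as share of 17 |
|---|---|---|---|---|
| 10% | 0 | 1.0 | 2.0 | 2/17 = 12% |
| 25% | 0 | 2.5 | 5.0 | 5/17 = 29% |
| 40% | 0 | 4.0 | 8.0 | 8/17 = 47% |

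If *g* is negative, the sign reverses and the benefit is understated. If CG loss is also informative, its own product is subtracted.

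**Cross-check with no true effect.** Suppose 45% of each whole group report fair or poor health at follow-up, a fraction d = 20% of the IG is unmeasured, and prevalence in that fraction is q. Attenders' prevalence is (0.45 − d·q)/(1 − d). For q = 65% this is (0.45 − 0.13)/0.80 = 40%, a spurious benefit of 5.0 points. With 80·0.80 = 64 IG and 80·0.90 = 72 CG members measured, a one-sided 5% test of follow-up prevalence rejects with probability Φ[(0.05 − 1.645·0.0850)/0.0848] = 14.5%. For q = 55% and 75% the spurious benefit is 2.5 and 7.5 points and the rejection rates are 8.8% and 22.3%. For q = 45% the bias is 0 and the rate is 5%. This compares follow-up prevalence alone. It carries over to the planned analysis of change only if absentees and attenders had similar baseline prevalence.

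**Numbers left to analyse.** With 10% loss, 80·0.90 = 72 are evaluable; with 25% IG loss, 80·0.75 = 60. With 72 in the CG, one-sided power for 45% against 28% is 68.5%, 66.0% and 63.1% at 10%, 20% and 30% IG loss. The loss of precision is modest; the possible bias matters more.

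**The case against.** The strongest reply is that the article is silent here rather than wrong. It says when the questionnaire is completed. It does not say that absentees are dropped or that nobody contacts them. Telephone numbers and trained researchers are available, the follow-up flow chart is not shown, and a full protocol may cover tracing. People who would have difficulty taking part for six months are excluded, which should reduce attrition. The planned tests use paired change, so poorer baseline health among those who stop is not enough to cause bias.

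Much of this stands, and it rules out several stronger readings that a reader might infer:
- *That absentees are not measured.* The text neither says so nor promises contact.
- *That the CG suffers only ordinary loss, or that the 10% is optimistic in the IG alone.* CG tracing is not described, and CG members may be lost as often or more often.
- *That the benefit is inflated.* Nothing in the article shows that those who stop fare worse; some may leave for reasons unrelated to health, or because they are well.
- *That every main outcome is affected.* Visits come from records.
- *That answers are given in a group at a farewell event.* The questionnaires are administered by researchers, and Table 1 is only an example, listing 19 sessions rather than 22.

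One thing remains. The timeline is detailed enough to give a fallback at baseline, and the single follow-up occasion that it states is conditional on attendance in one group only.

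**Conclusion.** The point holds as a risk of selection bias in the questionnaire outcomes (social support, GHQ-12, EQ-5D and the derived QALYs) and in the satisfaction ratings. It does not extend to primary care visits, and it does not establish that bias will occur. The documents give neither its size nor its direction. It is zero if non-attenders do not differ in change. It is 0-8 points, up to 47% of the assumed 17-point effect, if 10-40% of the IG are missing, their change is 0-20 points worse and CG loss is uninformative. All three conditions are assumptions; the 20-point upper value is larger than the planned effect and should be read as an outer bound. Because the risk comes from a stated procedure and is cheap to remove, it is worth correcting.

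**What to change.** In Participant timeline, replace the last-session rule with a statement that the follow-up questionnaire is sought from every enrolled person in both groups, within the same window around the end of the programme, whatever their attendance. Add that the trained researchers will contact IG members absent from the last session, using the telephone numbers already recorded and the attendance log to identify them, and that everyone is analysed in the original group.

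The cost is a number of extra calls or appointments for existing staff, and some answers given by telephone instead of in person. Recording the mode of each interview would let that difference be examined.

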**Fig. 1 Fig1:**
[figure not shown]
Flow chart of enrolment, allocation and follow-up

### Description of the intervention

The intervention “School of Health for Older People” consists of 22 weekly group sessions of 1.5 h each, in which issues related to health—including both biological and psychological issues—and social topics, are discussed. Attendance is free and the sessions will be held in community centers of the selected neighborhoods. In addition to helping participants learn about different health issues, the intervention encourages interaction among participants and works on skills in different fields, such as nutrition, management of emotions, self-medication, sexuality or physical activity. Furthermore, some sessions included visits to public spaces of the neighborhood and leisure activities adapted to older people.

Furthermore, most sessions are led by professionals who are experts on the topic covered and work in the neighborhood (professionals from the health services, social services, markets or neighborhood associations), making it easier to inform participants of the neighborhood’s available resources. The aim of the intervention is to decrease social isolation and loneliness and, therefore, to improve mental health, self-perceived health and wellbeing (see the explanatory model of the potential effects of the intervention in Fig. 2).

**Fig. 2 Fig2:**
[figure not shown]
Explanatory model of the potential effects of the “Schools of Health for Older People”

A brief description of the contents of one “School of Health for Older People” is shown in Table 1.

**Table 1 Tab1:** Example of the contents of sessions in the “School of Health for Older People”

Session 1	Introduction and group instructions. Colds and flu
Session 2	Adequate nutrition and fluid intake
Session 3	Elimination of body waste. Hygiene
Session 4	Laughter therapy
Session 5	Health hazards in the household and first aid
Session 6	Self-medication: the less the better
Session 7	Sexuality: enjoying it at any age
Session 8	Preventing scams and thefts
Session 9	Circus workshop
Session 10	Going out: how to do it in the safest way
Session 11	Memory and the five senses
Session 12	Emotions
Session 13	Physical activity at the park
Session 14	The value of older age
Session 15	How to become a volunteer at our neighborhood
Session 16	Our household remedies: let’s share!
Session 17	Diarrhea and Vomiting: what to do?
Session 18	Heat waves
Session 19	Songs of our times. Farewell

### Outcome measures

#### Qualitative evaluation

The main topics covered in the qualitative evaluation will be positive and negative aspects of the intervention, suggestions for its improvement, opinions on different session contents and logistic aspects of the intervention, and perceived benefits derived from the intervention.

#### Quantitative quasi-experimental design

##### Main outcomes

Social support will be measured through questions taken from the Medical Outcomes Study: Measures of Quality of Life Core Survey (MOS) [22] and NSHAP questionnaires [20]. Psychological morbidity will be measured through Goldberg’s General Health Questionnaire (GHQ-12) [23], and health-related quality of life will be measured through the EuroQoL (EQ-5D) questionnaire [24]. Objective information will be obtained on visits to the primary care center during the year before and after the intervention through access to the electronic records of the primary care centers.

All these variables will be measured simultaneously in individuals in the IG and CG. Data will be collected through baseline and post-intervention questionnaires administered by trained researchers.

##### Intervention-related variables

We will register attendance of participants at each session in the IG. Additionally, at the end of the School of Health, we will measure participants’ satisfaction with questions such as “please rate your general satisfaction with the School of Health from 0 to 10;”“ please rate your satisfaction with the speakers, place/space, frequency, schedule, and length of sessions from 0 to 10” “ Would you recommend the School of Health to a friend? ” These questions will be included in the post-intervention questionnaire.

##### Sociodemographic variables

Sociodemographic information will only be collected in the baseline questionnaire including the following variables: age, sex, marital status (single/ married/ divorced/ widowed), cohabitation status (living alone/living with someone else), educational level (illiterate /primary / secondary / university) and residential neighborhood.

#### Economic evaluation

The economic evaluation will be conducted from a health system (primary care) perspective, including direct costs of the program and the primary care health services used. The time frame will be 6 months and consequently no discounting will be applied to the calculations.

##### Costs

The costs of the program will be calculated based on the hourly wages of the public health professionals involved in the design and implementation of the intervention, obtained from the standard professional wages in the Official Gazette of the Catalan Government; the wages of the community nurses involved in the coordination and development of the workshops, obtained from the Catalan Institute of Health retributions report; and the costs of the venues and materials used throughout the intervention. The costs of the primary care medical and nurse visits either at the health center or at the patient’s home will be drawn from the Official Gazette of the Catalan Government on healthcare costs for the last published year.

##### Effects

The effects of the intervention will be measured in quality adjusted life years (QALY), through the EQ-5D questionnaire. Spanish tariffs will be used to estimate the utility of health states described by the participants. QALYs [25] will be assessed at baseline and at 6 months (end of the intervention), and QALYs will be calculated by multiplying utility by the amount of time a patient spent in a particular health state. Linear interpolation will be used for transitions between health states. QALYs will be assessed at baseline and at 6, 12 and 18 months.

### Data analysis

#### Qualitative evaluation

A thematic analysis will be carried out with the support of ATLAS.ti.software. In-depth-interviews and focus groups will be recorded and transcribed literally. Interviewers will keep a diary in which any reaction to events occurring during the research will be recorded.

The analysis will combine the inductive and deductive definition of codes. Preanalytical intuitions will be formulated after successive readings of the transcriptions and the observation notes. Next, three multidisciplinary investigators will create an initial analytical plan based on the most relevant topics (codification). The creation of categories by grouping the codes will be based on the criterion of similarity in relation to the objectives of the study and the emerging elements.

#### Quantitative quasi-experimental design

A descriptive analysis will be conducted to rule out significant differences between baseline characteristics (sociodemographic variables and outcomes studied) in the IG and the CG. The chi-square test will be used to compare qualitative variables. Continuous variables with normal distribution will be compared using the Student t test, and the Mann-Whitney U test will be used in non-normally distributed variables. In case of differences, a further multivariate effectiveness analysis will be conducted adjusting for these variables.

Further descriptive analyses will be conducted for results at baseline and at follow-up. Categorical outcomes will be described through percentages, and continuous outcomes will be described through mean scores and standard deviations or the median and interquartile range, as required. Differences between pre- and post-intervention measurements will be assessed and compared using the McNemar test, paired t-test, or sign test, according to the type of variable and distribution.

To assess the effectiveness of the intervention, a two-sample McNemar test will first be conducted to analyze differences in changes in pre- and post-intervention results between the IG and the CG for each main outcome. In those outcomes showing differences between the groups at the baseline measurement, Poisson regression models with robust variance will be built. In each model, the independent variables will be the group (IG or CG), the pre-intervention measurements for the outcome assessed and any relevant characteristics that differ between the groups at the baseline assessment.

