## Discussion

### Strengths and limitations

A potential limitation of the study is the length of follow-up, since the post-intervention measurements will be carried out immediately after the end of the intervention (6 months). Therefore, we will not be able to assess its long-term effects. Another limitation of the quantitative part of the study is that, because the design is quasi-experimental, there may be some differences between the IG and the CG. However, a statistical comparison of the main sociodemographic variables will be assessed and if any differences are found, they will be taken into account in the adjusted regression models.

A strength of the study is that, as far as we know, it is the first to assess the effectiveness and cost-effectiveness of an intervention focused on reducing social isolation in older people in deprived neighborhoods in an urban environment. Importantly, this is a multi-approach evaluation assessing the process, effectiveness and cost-effectiveness of an intervention while using mixed methods (quantitative and qualitative). Furthermore, the tests applied to measure the main outcomes (social support, psychological morbidity and health-related quality of life) are validated tests that not only allow for assessment of the potential impact of the intervention but also for comparison with other studies.

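### Covariate adjustment depends on baseline significance tests, with conflicting triggers, so in this non-randomised comparison small to moderate covariate imbalances will usually stay unadjusted

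*Protocol article*

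**What the plan says.** The Protocol article (Study setting and participants, quantitative design) has two intervention and two comparison neighbourhoods that "will be selected on a convenience basis, ensuring similar socioeconomic characteristics". There is no randomisation. About 80 people per group are expected, with the same share drawn from each recruitment setting.

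The Data analysis section for the quantitative design then gives three steps:

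- **First paragraph.** "A descriptive analysis will be conducted to rule out significant differences between baseline characteristics", covering both sociodemographic variables and the outcomes, by chi-square, t or Mann-Whitney tests. Then: "In case of differences, a further multivariate effectiveness analysis will be conducted adjusting for these variables".
- **Third paragraph, default.** Each main outcome is first analysed by a two-sample McNemar test of the pre-post changes, without covariates.
- **Third paragraph, model.** "In those outcomes showing differences between the groups at the baseline measurement, Poisson regression models with robust variance will be built". That model holds group, the outcome's baseline value and the characteristics that differ at baseline.

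The limitations text offers the same kind of rule as the answer to non-random groups: after a comparison of the main sociodemographic variables, "if any differences are found, they will be taken into account in the adjusted regression models".

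**The concern.** There are two problems.

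1. **The trigger is a significance test.** Without randomisation, confounding is the main threat to the effect estimate. A non-significant test with about 80 per group does not rule out a difference large enough to matter. When a covariate imbalance is missed, no adjustment for it follows. Whether a given outcome is reported from a change test or from a regression then turns partly on chance in the baseline sample.

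2. **The trigger is worded in two ways.** The first paragraph and the limitations text call for adjustment when any baseline variable differs, including sociodemographic ones. The third paragraph builds the model only for outcomes that themselves differ at baseline. Suppose the groups differ in age or cohabitation but an outcome is balanced at baseline. The first paragraph gives that outcome an adjusted analysis and the third does not. Two analysts could both follow the text and report different results.

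**Working it through.** **Inputs.** 80 per group at baseline, and 80 × 0.9 = 72 after the planned 10% loss (sample-size text). The reference prevalence is 0.45, since "45% of people aged 65 years or more in Barcelona reports fair or poor health". The effect is 17 points, since the plan "assumed that the intervention would reduce this prevalence by 17 points", so 0.45 falls to 0.28. Three inputs are not in the article and are assumed: a two-sided 5% level for the baseline screen, a one-sided 5% level for the outcome test unless stated (the article prints 0.05%), and a pre-post correlation φ of 0.3 to 0.6.

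**The plan's own figure.** The article gives no figure for the screen. Its only related figure is the sample size of 79 per group. With 0.45 v 0.28, one-sided 5% and 80% power, the usual two-proportion formula gives 99 per group, and 99/0.9 = 110 with loss, so 79 does not reproduce. That is a separate matter; nothing below uses 79.

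**Step 1: how often the screen flags a true imbalance.** For proportions p1 and p2 with mean p̄:

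power = Φ{[|p1 − p2| − 1.96·√(2p̄(1−p̄)/n)] / √([p1(1−p1) + p2(1−p2)]/n)}

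For 0.45 v 0.55 and n = 80: (0.10 − 1.96 × 0.0791)/0.0787 = −0.70, and Φ(−0.70) = 0.24.

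For a continuous variable differing by δ SD: power ≈ Φ(δ√(n/2) − 1.96). For δ = 0.3: Φ(1.897 − 1.96) = Φ(−0.063) = 0.475.

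| True imbalance, 80 per group | Chance flagged |
|---|---|
| 5 points (45% v 50%) | 0.09 |
| 10 points (45% v 55%) | 0.24 |
| 15 points (45% v 60%) | 0.48 |
| 20 points (45% v 65%) | 0.72 |
| 0.2 SD | 0.24 |
| 0.3 SD | 0.48 |
| 0.4 SD | 0.72 |

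For imbalances below 45% the chances are slightly higher (0.25 for 10 points, 0.50 for 15). Detection reaches 50% at about 15 points or 0.31 SD, and 80% at about 21 points or 0.44 SD. A 10-point imbalance is therefore missed about three times in four.

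**Step 2: what the default test already handles.** The change test compares (post − pre) between groups. A difference in the outcome that is the same before and after cancels. A covariate that affects the change does not cancel, and its bias is roughly the covariate imbalance times its effect on change. The article gives neither quantity, so this bias cannot be sized.

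**Step 3: change analysis against adjustment for the baseline outcome.** In a linear model, the baseline-adjusted group estimate is (post difference) − φ × (baseline difference) when pre and post variances are equal. The change estimate subtracts the whole baseline difference. Take an intervention group 10 points healthier at baseline and no effect:

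- *The difference is stable.* The post difference is −0.10. The change estimate is 0. The baseline-adjusted estimate is −(1 − φ) × 0.10 = −0.07, −0.05, −0.04 at φ = 0.3, 0.5, 0.6.
- *Follow-up depends only on the baseline value.* The post difference is −φ × 0.10. The baseline-adjusted estimate is 0. The change estimate is +(1 − φ) × 0.10 = +0.07, +0.05, +0.04.

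Simulation at 72 per group used a z-test on the difference in mean change to stand for the two-sample McNemar test, and a robust linear model on group and baseline value to stand for the regression:

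| Setting | φ = 0.3 | φ = 0.5 | φ = 0.6 |
|---|---|---|---|
| Groups truly balanced, 17-point effect, one-sided 5%: power of planned rule v always adjusting | 56% v 72% | 68% v 79% | 77% v 85% |
| Gain from adjusting (points) | 16 | 11 | 8 |
| Stable 10-point difference, no effect, one-sided 5%: false rejection, change test v always adjusting | 5% v 22% | 5% v 17% | 5% v 14% |
| Follow-up depends on baseline, 10-point difference, true effect −0.17: mean estimate, planned rule v always adjusting | −0.134 v −0.170 | −0.143 v −0.169 | −0.149 v −0.170 |

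With a two-sided 5% outcome test, the gain under balance is about 10 to 18 points.

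**The case against.** **The default test is not blind to baseline.** It analyses changes, so a reader who infers that most real imbalances go uncorrected is claiming more than the plan supports. For the outcome's own baseline, a stable difference is removed. For covariates, being missed more often than not holds only below about 15 points or 0.31 SD. This stands, and it limits the point to small and moderate covariate imbalances.

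**Adjusting for the baseline outcome is not uniformly better.** A reader might infer from the power figures that the plan discards power and that the regression should simply replace the change test. Those figures assume truly balanced groups, which this design does not guarantee. With a stable pre-existing difference, the regression is the biased method. The article does not say which situation applies, so demoting the change test is not supported.

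**An outcome balanced at baseline would not necessarily go unadjusted.** That follows from the third paragraph alone; the first paragraph and the limitations text point the other way. The defect is the conflict between them.

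**The design limits imbalance.** Neighbourhoods are matched on education, unemployment and income, and recruitment settings are balanced. The article also discloses that the groups may differ and already specifies an adjusted model. This lowers the severity. It does not rescue the trigger, because the residual differences that matching leaves are likely to be in the range that the screen misses.

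**Conclusion.** The point holds in limited form and should be fixed, though it does not invalidate the plan. Adjustment is tied to baseline significance tests and the text conflicts on what triggers it. At 80 per group the screen flags a 10-point imbalance about 24% of the time and a 0.3 SD imbalance about 48%, so smaller covariate imbalances will usually go unadjusted. The exposure is to covariates that affect change. The detection figures rest on an assumed two-sided 5% screen. The comparison of estimators rests on assumed correlations of 0.3 to 0.6 and on approximations to both planned methods. The size of the resulting bias in this trial cannot be derived from the article.

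**What to change.** - Drop the baseline tests as a trigger and describe balance by standardised differences.
- For every main outcome, fit a covariate-adjusted analysis with a fixed set, whatever the baseline comparison shows: age, sex, cohabitation and education (all in the baseline questionnaire) and recruitment setting (known from recruitment).
- Report two estimates with that covariate set: the adjusted between-group difference in change, and the model adjusted for the outcome's baseline value. Name one as primary before the outcome comparison is run and state its assumption. The change analysis assumes that the group difference would have stayed constant without the intervention. The baseline-adjusted model assumes that people with equal baseline values and covariates would have had the same expected follow-up in either group.
- Align the first and third paragraphs of the analysis section and the limitations text with this rule. The unadjusted two-sample McNemar test can stay as supporting information.

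The cost is rewording, a few degrees of freedom for covariates and a second reported estimate per outcome. No new data are needed.
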